### Data coding and storage

The questionnaires will be completed electronically (on www.alchemer.eu) by the participants. Data encoding will be done automatically by Alchemer and will be regularly checked by one of the principal investigators. Final databases will be stored on a protected server from the University of Liège, protected by a password, only accessible to the principal investigators. Data coding and storage comply with the European General Data Protection Regulation (GDPR).

## Discussion

Recent studies highlighted the prevalence and negative consequences of the PNSC in oncology [1–3]. The core symptom of this cluster could be of major importance in the management of the cluster of symptoms as a whole [22] but it is still unclear which symptom from the cluster is the most central among patients with breast or digestive cancer. Determining this core symptom could allow to develop more cost-effective interventions, as addressing this symptom will likely decrease the other symptoms from the cluster [1–3, 11, 17, 18, 20, 23]. The development of multi-component interventions, especially those aiming to manage the whole PNSC, is then urgently needed in oncology [11]. We thus designed a longitudinal study assessing the PNSC and other symptoms in breast cancer and digestive cancer survivors, over 2 years. We hypothesize that: (1) one dimension of CRF or of emotional distress (i.e., depression or anxiety) will be the core symptom in all the obtained networks (i.e., for both cohorts and at each of the four measurement times), (2) the physical and mental dimensions of CRF will have different relationships with the other symptoms of the networks (e.g., physical fatigue could have stronger relationships with other physical symptoms such as loss of appetite or nausea/vomiting), (3) the configuration of the networks will differ according to the cohort considered (e.g., nausea/vomiting and diarrhoea/constipation could have stronger relationships with CRF, anxiety or depression in the digestive cancer cohort), and the measurement time (e.g., some correlations could weaken over time, as the intensity of some symptoms will decrease and became less important in the networks), and (4) self-compassion and coping strategies will not significantly evolve over time, even if a trend in this sense is possible due to a better adaptation to cancer.

The present study will suffer from several limitations. First, as no standard procedure to determine the ideal sample size for network analyses exist, we based our calculation on existing studies with similar methodology. It is then possible that the sample size will remain too small to allow robust results. Second, we decided to include patients who completed their active treatment within the last 5 years. One could argue that 5 years is a rather long period of time, that the psychological state and quality of life of patients are very likely to evolve during that time, and that the participants would be very different from each other, leading to an unexpected heterogeneity of our sample. However, the threshold of 5 years is commonly used in oncology studies, as it is considered to distinguish the “short-term” and “long-term” cancer survivors [2, 35, 48]. Our decision is thus in line with existing practices in the field. Finally, we will focus on two populations of cancer patients only (i.e., survivors of breast or digestive cancer). These results will then be relevant to these patients only. However, breast and digestive cancers are among the most frequent cancers [38], making our results applicable for many patients and health professionals.

Despite these limitations, this study will be one of the first to assess over a long period of time the evolution of the PNSC on two distinct populations. As described, the conduction of the present study will allow us to design a new multi-component intervention specifically targeting the core symptom determined in each cohort, and to assess its feasibility and preliminary benefits. Taken as a whole, this project is thus particularly original, timely relevant and innovative. It will bring new knowledge about the PNSC, its evolution, and its specificities according to the diagnosis, and its results will open a lot of scientific and clinical perspectives to improve symptom (self-)management of patients with cancer.

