## Methods

### Design and procedures

We designed a longitudinal observational study to assess the evolution of the PNSC and the respective relevant variables in two distinct cohorts of cancer survivors (breast cancer survivors and digestive cancer survivors). Questionnaires (in French; see “Statistical analyses”for more details) will be completed online (on www.alchemer.eu) at four different times: at inclusion (T1), then 6 (T2), 12 (T3) and 24 (T4) months later. Written informed consent will be obtained from each participant at the beginning of the study (included at the beginning of the online questionnaires), and the inclusion criteria are checked at the beginning of the questionnaires, so that only participants who meet the criteria will be eligible to complete them. Participants will also have the possibility to contact the principal investigators by email or phone if needed (e.g., question, adverse event, or difficulty related to the study). At each measurement time, the risk of missing responses is very low, as the online questionnaires are designed in a way that does not allow for missing answers. The short duration of the questionnaires (approximately 20 min) will also increase completion and retention. All data will be anonymized: a code will be attributed to each participant and used during the entire study. Only the principal investigators involved in this study will have access to the complete datasets. Review of the trial process and difficulties encountered are discussed regularly between the researchers involved. As no standard procedure to determine the ideal sample size for network analysis is commonly used, the number of participants required in this study will be based on other studies in oncology using similar methodology [1–3, 17, 18, 20] and including between 172 and 342 patients per cohort, and set to 200. Accounting for a drop-out rate of 10% at one year in an observational study [36], and likely a higher drop-out rate at two years, we aim to include 240 participants in each cohort.

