### Assessments

Approximate duration of questionnaires completion is 20 min at each measurement time. First, socio-demographic and medical data will be collected (i.e., sex, age, marital situation, education level, professional activity, cancer diagnosis, cancer stage, personal history of cancer and treatments, possible recurrence during the study, comorbidities, neurological and psychiatric history, history of drug or alcohol abuse, previous participation in a mind-body intervention, psychotherapy, major life events). Symptoms involved in the PNSC, as well as other common symptoms and QOL, will be assessed as follows:

*European Organization for Research and Treatment of Cancer - Quality of Life Core Questionnaire-30 (EORTC QLQ-C30)* [40]: This questionnaire (30 items) assesses the QOL of patients with cancer through 5 functional scales (physical, role, emotional, cognitive, and social functioning), three symptom scales (fatigue, nausea and vomiting, pain), a global health status/QOL scale and several single items for additional difficulties (dyspnoea, insomnia, appetite loss, constipation, diarrhoea, financial difficulties). Each item is scored on a 4-point Likert scale (‘not at all’ to ‘very much’), excepted for the global health status/QOL that is a 7-point scale (‘very bad’ to ‘excellent’). For functional scales and QOL scale, higher scores indicate better functionality and QOL. For symptom scales and single items, higher scores indicate higher symptomatology.*Multidimensional Fatigue Inventory (MFI-20)* [41]: This 20-item scale is designed to measure fatigue on 5 dimensions: general fatigue, physical fatigue, mental fatigue, reduced motivation and reduced activity. Suggested cut-off scores for significant general fatigue have been proposed for the general population: ≥ 11 (for men between 40 and 59 years-old), ≥ 12 (for women between 40 and 59 years-old), and ≥ 14 (for men and women older than 60 years-old) [42, 43].*Hospital Anxiety and Depression Scale (HADS)* [44]: This 14-item scale measures anxiety and depression, and has been validated for people with somatic illnesses. Scores between 8 and 10 on a dimension suggest the presence of anxious and/or depressive disorders, while scores between, 11 and 21 indicate the presence of such disorders.

Other variables of interest (i.e., coping strategies and self-compassion) will be assessed as follows:

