### Statistical analyses

Normality of data will be checked using Shapiro-Wilk test. Sociodemographic and medical data will be described using frequencies and percentages, means and standard deviations, or medians and interquartile ranges, depending on the distribution. To estimate the networks’ structure, a standardized score (z score [1]) will be calculated for each variable or dimension. Three centrality indices will be used: strength (number and strength of the direct connections to a node/symptom, i.e., sum of absolute weights; a high strength means that the symptom is more likely to occur in conjunction with other symptoms), closeness (node’s relationship to all other nodes; closer nodes mean stronger correlation), and betweenness (importance of a node in the average pathway between other pairs of nodes; a node with a higher betweenness has greater influence in the network) [1, 2]. Symptom networks will be created for both cohorts, at each of the four measurement times. To assess the differences between two networks (i.e., between breast and digestive cancers), and over time for each cohort (i.e., between T1, T2, T3 and T4), network comparison tests will be used [1, 17]. The evolution of the other variables over time (i.e., self-compassion, self-care agency, self-care strategies already implemented to manage CRF, and the representations about CRF) will also be measured and compared through repeated measures MANOVA and post-hoc comparisons.

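### Hypothesis 4 predicts no significant change in self-compassion and coping, but the only stated over-time test cannot support stability

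*Protocol article*

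**What the plan says.** The Discussion lists four hypotheses. The last is that "self-compassion and coping strategies will not significantly evolve over time, even if a trend in this sense is possible", with better adaptation to cancer offered as the reason for such a trend.

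In Methods, Assessments, the variables concerned are introduced with "Other variables of interest (i.e., coping strategies and self-compassion) will be assessed as follows". The instruments are a coping checklist with three dimension scores and a self-compassion scale with six dimensions and a total mean score.

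Under Statistical analyses, the matching sentence begins "The evolution of the other variables over time (i.e., self-compassion, self-care agency, self-care strategies already implemented to manage CRF, and the representations about CRF" and says that these "will also be measured and compared through repeated measures MANOVA and post-hoc comparisons". Coping is not in that list; self-compassion is the only variable common to it and to the Assessments definition.

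Under Design and procedures, measurements are taken "at inclusion (T1), then 6 (T2), 12 (T3) and 24 (T4) months later". The per-cohort size is drawn from earlier oncology network studies, "including between 172 and 342 patients per cohort, and set to 200". The allowance for loss is described as "Accounting for a drop-out rate of 10% at one year in an observational study [36], and likely a higher drop-out rate at two years". The resulting recruitment target is 240 per cohort. The article gives no margin, smallest change of interest or power for self-compassion or coping.

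**The concern.** The research hypothesis coincides with the null hypothesis of the planned test. A MANOVA can give evidence that scores changed. Failing to reject shows only that no change was detected, which can happen because there was none or because the data were too few or too noisy.

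The prediction is worded in terms of significance, so failing to detect a change is enough to meet it as written. Losing participants makes this easier, whereas evidence for stability ought to get harder to obtain as data are lost. The trend clause loosens the prediction further, since a flat course and a non-significant drift both fit.

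At stake is whether the study can say that self-compassion and coping stay stable over two years in these survivors. The Background names self-compassion learning and adaptive coping as possible components or targets of interventions, so later work may draw on that statement. It should rest on how large the change is.

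**Working it through.** **The plan's own figure.** Inflating 200 for 10% drop-out gives 200/(1 - 0.10) = 222.2, so 223. The stated 240 corresponds to 1 - 200/240 = 16.7% drop-out. That is compatible with the higher but unquantified two-year rate, so 240 can be neither confirmed nor called wrong. It was not set for hypothesis 4. I take 200 completers per cohort as the plan's target, and 150 (drop-out 1 - 150/240 = 37.5%) as a less favourable case.

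**Assumptions not in the documents.** Two-sided alpha 0.05; within-person correlation r of 0.5 to 0.7; equal SD at each time; true changes of 0.10 to 0.30 baseline SD; one score in one cohort.

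**Step 1. Paired T1-T4 contrast.** The standard error in SD units is sqrt(2(1 - r)/n). With n = 200 this is sqrt(1.0/200) = 0.0707 at r = 0.5 and sqrt(0.6/200) = 0.0548 at r = 0.7. For a change of 0.10 SD the noncentrality is 0.10/0.0707 = 1.41 or 0.10/0.0548 = 1.83. The noncentral t gives power 0.29 or 0.44, so the change is missed 71% or 56% of the time.

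**Step 2. Four-time test.** This is closer to the planned analysis: a one-variable repeated measures Hotelling test with 3 and n - 3 degrees of freedom, assuming mean changes of 0, d/4, d/2 and d at T1 to T4 and equal correlations. The noncentrality is n x d² x 0.547/(1 - r), where 0.547 is the sum of squared deviations of (0, 0.25, 0.5, 1) from their mean. For d = 0.10 and n = 200 it is 2.19 (r = 0.5) or 3.65 (r = 0.7), giving power 0.20 or 0.32.

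Chance of a non-significant result despite a real change, 200 completers (r = 0.5 / r = 0.7):

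| True T1-T4 change | Paired contrast | Four-time test |
|---|---|---|
| 0.10 SD | 71% / 56% | 80% / 68% |
| 0.15 SD | 44% / 22% | 57% / 34% |
| 0.20 SD | 20% / 5% | 31% / 10% |
| 0.30 SD | 1% / under 1% | 3% / under 1% |

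**Step 3. Effect of attrition.** At 150 completers the four-time test misses a 0.20 SD change 45% / 21% of the time, against 31% / 10% at 200.

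**Step 4. What a margin-based rule could deliver.** Stability is declared if the 90% confidence interval lies inside ±M. With no true change, power is approximately 2Φ(M/SE - 1.645) - 1, or zero if that is negative. For M = 0.20 and r = 0.7: 0.20/0.0548 - 1.645 = 2.01, giving 0.955.

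| Illustrative margin | Power at 200 completers (r = 0.5 / 0.7) | Completers for 80% power (r = 0.5 / 0.7) |
|---|---|---|
| 0.10 SD | 0% / 14% | 857 / 514 |
| 0.15 SD | 37% / 73% | 381 / 229 |
| 0.20 SD | 76% / 96% | 215 / 129 |
| 0.30 SD | 99% / 100% | 96 / 58 |

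The 90% half-width at 200 completers is 1.645 x 0.0548 = 0.09 to 1.645 x 0.0707 = 0.12 SD. If self-compassion and all three coping scores must pass at the 0.20 SD margin, and they are treated as independent, power falls to 0.763⁴ = 34% (r = 0.5) or 0.955⁴ = 83% (r = 0.7).

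**The case against.** **No confirmation rule is written down.** A reader might infer that the plan counts p above 0.05 as proof of stability. The article states neither an alpha nor such a rule, and it does not call the scores stable. Reporting of intervals may be left to an SAP that is not shown. This stands as a limit on the claim. It does not remove the point: the hypothesis itself is phrased by significance, and an SAP that tests it as worded inherits the problem.

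**Coping is not in the MANOVA list.** It would be too strong to say that the whole of hypothesis 4 is judged by the MANOVA, because the link is explicit only for self-compassion. This also stands, but it leaves the coping half of the hypothesis with no named test.

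**An equivalence rule has its own uncertain zone.** With 200 completers, r = 0.7, a 0.20 SD margin and a true change of 0.10 SD, it declares stability Φ(0.10/0.0548 - 1.645) = 57% of the time. So the argument for it is not that intermediate changes become easy to classify. It is that the chance of declaring stability when the true change is at or beyond the margin is held to 5%, and that losing data makes the claim harder to reach.

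**The stakes are modest.** This is the last of four hypotheses, its variables are followed in parallel to the main aim, and what is carried forward is chiefly the core symptom. That is correct, and it bounds the importance.

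**Conclusion.** The point holds in a limited form. As worded, hypothesis 4 is met by failing to find a change, and the one stated over-time analysis cannot supply evidence for stability. A small real change of 0.10 SD would go undetected more often than not under every assumption tried (56% to 80%). A change of 0.30 SD would be missed 3% of the time or less with 200 completers, so a large shift is unlikely to pass unnoticed.

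These figures rest on an assumed alpha, correlation and number of completers, and the four-time results also on an assumed course of change. A multivariate test across several scores would give other values.

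One might also infer that the study is large enough to demonstrate stability. The documents do not support that: it depends on a margin nobody has set, on the correlation, on two-year retention, and on whether every score must pass. The network objectives are untouched.

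**What to change.** 1. Restate hypothesis 4 in terms of the size of the T1-T4 mean change in self-compassion and in each coping score, and delete the trend clause.
2. Name coping in the over-time analysis under Statistical analyses, so that the list matches the definition in Assessments.
3. Report each change with its confidence interval, per cohort.
4. Pre-specify and justify a margin. Claim stability only if the 90% confidence interval lies inside it; otherwise report change or an inconclusive result. State whether the claim is made score by score or requires all scores. The 0.20 SD used above is an illustration, not a recommendation.

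This changes wording and analysis only, with no new participants, visits or questionnaires. The real cost is that the sponsor must commit to a margin before seeing the data and accept that the answer may be inconclusive, particularly with a tight margin or heavy two-year drop-out.

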## Data Availability

The datasets used during the current study will be available from the corresponding author on reasonable request ([contact]).
